### Participants and recruitment

The approach will be partially randomized. Participating schools from two Cologne districts (Chorweiler and Meschenich) will be recruited for this study. The two districts have been chosen because of their social circumstances, as defined by the Cologne Office for Urban Development and Statistics [15]. The index for social circumstances of urban districts is based on information related to issues such as economic deprivation, political and cultural disadvantage, and health inequality. With the support of the district coordinators responsible for social planning, two elementary schools (one in each district) will be recruited, and local networks will be identified. The elementary schools will provide access to the target group of children, parents, teachers and other pedagogical staff. Any children and parents at the chosen elementary schools will have the opportunity to participate; therefore, the target group will be composed randomly. The identified networks will be used to get in contact with local stakeholders to establish participatory collaborations.

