**Fig. 1 Fig1:**
[figure not shown]
Study Design of the StuPs Project

The intention of the second period (Period II) is to implement the developed measures over a 27-month period. Measures will be combined with existing health-related structures in terms of health in all policies. To evaluate efficacy, the status quo will be analyzed in a manner equal to that in Period I to capture changes on structural levels. To investigate behavioral changes, pre- and post-tests of the children’s physical literacy levels will be conducted. Additionally, the German Federal Ministry of Health has employed an external evaluation group [6], to investigate promoters and inhibitors during the StuPs project in the context of the call for funding “Bewegung und Bewegungsförderung”. The aim of the external evaluation is to detect factors of success within community-based approaches. At the end of Period II, a transfer guideline will be developed through an iterative and participatory process to be provided to various districts and communities; this transfer guideline will contain step-by-step instructions, serving as a best practice model, using as few resources as possible. Additionally, it will include information on how to i) capture needs and wants in terms of capacity building and physical literacy promotion in settings, districts, or communities; ii) apply and implement measures; ii) evaluate efficacy; and iv) document procedures to facilitate learning from each other regarding practical experiences. Throughout the entirety of the project, there will be cyclical, iterative reports and dialogues at the community level.

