### Intervention mapping

Intervention mapping describes the combination of theory- and evidence-based approaches in a bottom-up procedure containing six steps [16]. Through these six steps, interventions can be designed that are appropriate to the target group and also consider healthy environments [17]. The StuPs project is designed to follow the six stages (Table 1). The target group will be integrated in the identification of needs, wants and development of measures. Additionally, current scientific knowledge and existing behavioral theories will be researched and considered. The six steps of the intervention mapping form the modular structure of the project and emerge in specific work packages.

**Table 1 Tab1:** Modified Steps of Intervention Mapping within the StuPs Project [16]

Step 1: Assessment of needs, wants and inventory of health-related issues to identify current conditions in terms of capacity building and physical literacy promotion in the selected districts.	
Step 2: Goal specification within the settings/networks with stakeholders in light of the knowledge generated in step 1.	
Step 3: Scientific literature research and comparison with previous results of community-based approaches as well as definitions and instruments to investigate physical literacy, aiming to accompany the theoretical approach with existing knowledge.	
Step 4: Derivation and development of school- and district-related measures based on the knowledge of the previous steps. In this step, the content for the measures conducted later will be created.	
Step 5: Definition of further procedures and implementation of the measures created previously.	
Step 6: Review, evaluation, and development of transfer indicators.	

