### Data management and analysis

Any conducted assessments will be carried out anonymously. The results of Period I will be analyzed and interpreted by conducting qualitative data analysis [18] in the MAXQDA 2020 software. The data resulting from the children and parental pre- and post-tests will be analyzed using the SPSS software version 27.0 (SPSS Inc., Chicago, IL, USA). The significance level α will be set at < .05; confidence intervals will be estimated at 95%. Descriptive analysis will be conducted to identify cross-sectional and long-term changes in physical literacy level, including motor skills, by generating means and variances. Additionally, correlations and influencing factors among variables will be assessed using analysis of covariance and regressions.

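### The protocol article calls the study partially randomized and its target group randomly composed, but it describes no random sampling or allocation step, only purposive sites and voluntary participation

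*Protocol article*

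**What the plan says.** The section Participants and recruitment opens its description of the design with "The approach will be partially randomized". It then sets out how each level of the sample arises:

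- **Districts:** "The two districts have been chosen because of their social circumstances", as measured by a city index. Both are named.
- **Schools:** "With the support of the district coordinators responsible for social planning, two elementary schools (one in each district) will be recruited".
- **Children and parents:** "Any children and parents at the chosen elementary schools will have the opportunity to participate; therefore, the target group will be composed randomly".

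On the comparison, the Study design section says "To investigate behavioral changes, pre- and post-tests of the children" (continuing with their physical literacy levels). The abstract likewise names a pre/post design for assessing efficacy. Table 1, under Intervention mapping, places the measures at group level: "Derivation and development of school- and district-related measures based on the knowledge of the previous steps". Data management and analysis sets a significance level of .05 and 95% confidence intervals. It names descriptive statistics, analysis of covariance and regressions.

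**The concern.** The word random carries two technical meanings in a trial plan: units are drawn by chance from a population, or units are allocated by chance to conditions. The article uses it in both directions, once for the approach and once for the target group, yet the steps it describes fit neither meaning. The reason it gives for the second use is the openness of the invitation. Openness determines who may take part. Who does take part is then decided by the families, and those who respond may well differ from those who do not, for instance in engagement or activity.

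What is at stake is the classification of the study. Readers and evidence synthesists use the randomization label to judge what a study can show. A partly randomized study invites a causal reading of its result, and a randomly composed sample invites reading its intervals as those of a chance sample of the schools' families. The results are also meant to feed a transfer guideline for other districts, so a wrong account of how the sample arose would travel with it.

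**Working it through.** The article states no sample size, participation rate, allocation ratio or power, so there is no figure to reproduce. The check is to go through each point at which chance could enter and ask whether the article describes a chance mechanism there.

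| Step | What the article describes | Chance mechanism described |
|---|---|---|
| Choice of districts | Two named districts, chosen on a social index | None |
| Choice of schools | One per district, recruited with coordinators' help | None |
| Children and parents | Open to all at the two schools, who opt in | None |
| Allocation to conditions | Pre/post evaluation; no comparison arm described | None |

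The count is zero of four.

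The article's inference about the target group can also be tested on its own. The premise is that everyone at the schools "will have the opportunity to participate; therefore, the target group will be composed randomly" is the conclusion drawn from it. The conclusion would follow if participants were then drawn by lot, or if everyone took part (a census, which is also not a random sample). Neither is stated. What follows from the premise is voluntary participation.

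**Illustration of what self-selection could do.** All inputs here are assumptions, because the documents give none of them. Let *d* be the difference in mean score between volunteers and non-volunteers, and *p* the participation rate.

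- Error of the volunteer mean as an estimate of the school mean: (1 − *p*) × *d*.
  - *p* = 0.6, *d* = 0.3 SD: 0.4 × 0.3 = 0.12 SD.
  - *p* = 0.3, *d* = 0.5 SD: 0.7 × 0.5 = 0.35 SD.
- Apparent change with no true change, if participation moves from *p*₁ at pre-test to *p*₂ at post-test with *d* constant: (*p*₁ − *p*₂) × *d*.
  - 0.6 to 0.4, *d* = 0.3 SD: 0.2 × 0.3 = 0.06 SD.
  - 0.6 to 0.4, *d* = 0.5 SD: 0.2 × 0.5 = 0.10 SD.

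The second result needs unpaired samples of different composition at the two tests. If the same children are tested twice and analysed as pairs, a constant level difference between volunteers and non-volunteers drops out of the change score. If participation rises instead of falling, the sign reverses. The article says that assessments are anonymous and does not say whether a child's two tests can be linked, so it does not settle which case applies.

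**The case against.** The case on the other side has four parts.

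1. **A random step may exist out of sight.** The article does not say how the one school in each district is picked, and the study design figure is not available. A reader might infer from the text that nothing at all is randomized. The documents do not support going that far: they support only that no random step is described. This stands, and the correction must leave room for it. It does not rescue the sentence on the target group, because even schools drawn by lot would not make families who opt in a random sample.

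2. **The real procedure is disclosed.** The same paragraph states openly how districts, schools and families come in, the abstract speaks only of a pre/post design, and no named analysis compares randomized arms. Nor does the article claim that the sample represents the district. This is fair: correcting the label changes no stated analysis. It limits the harm, but it also shows that the label contradicts the text around it.

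3. **The SD figures have no basis in the documents.** This stands. A reader might take them as an estimate of the bias in this study. They rest wholly on assumed rates and an assumed gap, and the change figures also need unpaired samples.

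4. **Weighting would not cure the problem.** Weighting to the school roll by grade and sex leaves selection on motivation or activity untouched within each grade and sex. This also stands, so weighting should not be a required part of the correction.

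One could add that a journal article leaves detail to a fuller document. That does not help here. The article gives its own reason for the word random, and further detail cannot make that inference valid. The absence of a control group, with children maturing over a 27-month period, is a separate matter and carries no weight in this point.

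**Conclusion.** Both statements are wrong as written. The described design is a pre/post study at two purposively chosen districts, in schools recruited through coordinators, with voluntary participation. Partial randomization is unsupported by any described step, and random composition is inferred from a premise that does not yield it.

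The conclusion rests on the article's text alone and on one modest reading, that being offered the opportunity to take part means participation is voluntary. It does not depend on the numerical illustration. The size of any selection bias in this study is unknown and cannot be derived from the documents. What changes is what the study can claim: its findings describe participants at two schools, and its intervals should not be presented as resting on random sampling or allocation.

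**What to change.** Replace both sentences in Participants and recruitment with: *The study is a non-randomised pre/post study; districts are purposively selected, schools are recruited through district coordinators, and participation is voluntary.*

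If a random step does exist, state its unit and mechanism instead, and still delete the claim that the target group is composed randomly.

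Also:

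- Report participation at each test against the school roll, so that readers can see how selective the sample is and whether it shifts between tests.
- Limit conclusions to participants at the two schools.
- Treat weighting to the roll by grade and sex as optional. If it is used, say that it does not correct selection on motivation or activity.

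The cost is a less favourable description of the design, two sentences of text, and an aggregate head-count from each school at each test, which schools can be expected to hold. No stated analysis has to change.

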### Intervention mapping

Intervention mapping describes the combination of theory- and evidence-based approaches in a bottom-up procedure containing six steps [16]. Through these six steps, interventions can be designed that are appropriate to the target group and also consider healthy environments [17]. The StuPs project is designed to follow the six stages (Table 1). The target group will be integrated in the identification of needs, wants and development of measures. Additionally, current scientific knowledge and existing behavioral theories will be researched and considered. The six steps of the intervention mapping form the modular structure of the project and emerge in specific work packages.

**Table 1 Tab1:** Modified Steps of Intervention Mapping within the StuPs Project [16]

Step 1: Assessment of needs, wants and inventory of health-related issues to identify current conditions in terms of capacity building and physical literacy promotion in the selected districts.	
Step 2: Goal specification within the settings/networks with stakeholders in light of the knowledge generated in step 1.	
Step 3: Scientific literature research and comparison with previous results of community-based approaches as well as definitions and instruments to investigate physical literacy, aiming to accompany the theoretical approach with existing knowledge.	
Step 4: Derivation and development of school- and district-related measures based on the knowledge of the previous steps. In this step, the content for the measures conducted later will be created.	
Step 5: Definition of further procedures and implementation of the measures created previously.	
Step 6: Review, evaluation, and development of transfer indicators.	

### Community-based participatory research

The CBPR approach developed by Israel et al. [9] has been decisive in designing the content of the StuPs project. CBPR aims to promote health equity, strategies development, empowerment of a target group, and capacity building within the targeted community [9]. This approach intends to combine scientific, practical, and policy stakeholders as well as different professions. Therefore, the StuPs approach is characterized by a high level of practical orientation to strengthen participatory collaborations between science, practice, and policy. To this end, the CBPR principles by Israel et al. [9] have been modified to promote individual and collective empowerment and the development of expertise and structures in terms of capacity building and physical literacy (Table 2).

**Table 2 Tab2:** Modified Principles of the Community-Based Participatory Research following Israel et al. [9]

(1) The network sees itself as a unit.	
(2) The network builds on existing strengths and resources.	
(3) The network works transparently and in partnership.	
(4) The network promotes joint development, empowerment, and capacity building.	
(5) The network creates a balance between knowledge generation and interventions for the mutual benefit of all partners.	
(6) The network focuses on specific needs in the context of physical activity promotion, taking into account sociodemographic and gender characteristics as well as systematic geographical data.	
(7) The development of measures and implementation strategies takes place in a cyclical, iterative, and reflexive process.	
(8) All results and developments will be made accessible to all partners; further dissemination and use will also take place in coordination.	
(9) The aim is to create the basis for long-term cooperation and the establishment of the topics as a cross-sectional task of all partners involved (health in all policies), with the intention of sustainably promoting the physical activity (and health) and physical literacy of vulnerable groups.	

### Data management and analysis

Any conducted assessments will be carried out anonymously. The results of Period I will be analyzed and interpreted by conducting qualitative data analysis [18] in the MAXQDA 2020 software. The data resulting from the children and parental pre- and post-tests will be analyzed using the SPSS software version 27.0 (SPSS Inc., Chicago, IL, USA). The significance level α will be set at < .05; confidence intervals will be estimated at 95%. Descriptive analysis will be conducted to identify cross-sectional and long-term changes in physical literacy level, including motor skills, by generating means and variances. Additionally, correlations and influencing factors among variables will be assessed using analysis of covariance and regressions.

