**Methods:**

The project is built upon the intervention mapping approach and consists of two periods with an overall duration of 3 years. Period I will last 9 months and include an assessment of needs, wants, strengths, and weaknesses regarding physical activity and health promotion at the community- and school-based level according to the keywords “capacity building” and “physical literacy.” Based on the knowledge gained in this stage, measures for capacity building to promote healthy lifestyles and physical literacy in children will be developed using the community-based participatory research and capacity building approach. In Period II, the measures will be applicated, implemented and evaluated using a pre−/post-design to assess efficacy.

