## Background

Increasingly sedentary behavior in children constitutes a growing global challenge, although awareness of the role of physical activity in optimizing children’s health is ubiquitous [1, 2]. Despite the various health benefits of physical activity on physical, psychosocial, cognitive, motor skill, and language development [3], only 20% of children and adolescents worldwide meet the World Health Organization (WHO)‘s physical activity recommendations of 60 min per day [2]. Similar data resulted from a German health survey from 2014 to 2017 conducted by the Robert Koch Institute: only 22.4% of girls and 29.4% of boys met the WHO’s recommendations [4] - a far cry from the German physical activity recommendations of 90 min or more per day among elementary school children [5]. These data have also shown that time spent physically exercising correlates positively with socioeconomic status and negatively with age. Therefore, the challenge remains to develop efficient and sustainable strategies for promoting physical activity among children. The StuPs project: a school- and community-based participatory approach for promoting physical activity in children and their families, was developed for this purpose, particularly in response to “Bewegung und Bewegungsförderung” (“exercise and physical activity promotion”), the German Federal Ministry of Health’s call for funding [6]. The aim of this call was to spread the knowledge of the German recommendations for physical activity in the sense of health in all policies. Currently, there is no gold standard for promoting physical activity in young children, especially among vulnerable groups; despite this, school-based and multicomponent approaches are suspected to be most efficient. Because schools are the optimal environment for reaching a great number of youth demographics, school-based approaches seem to have high efficacy [5]. However, physical activity promotion in schools seems to have a limited impact on children’s movement behavior during their leisure time [7]. Current evidence assumes greater success in preventing childhood obesity if entire communities are involved in creating and promoting healthy environments [8]. The inclusion of additional out-of-school aspects within the scope of multicomponent approaches and the inclusion of families, communities, policies, and stakeholders in a participatory manner is recommended [5, 7]. Participatory approaches, such as community-based participatory research (CBPR) [9], have the potential to generate synergy, reach greater acceptance within the target group, and engender increased engagement [8, 10], especially in combination with capacity building [8, 11]. On a behavioral level, the available evidence supports an approach that promotes physical literacy, a construct that indicates the basis for an active lifestyle and serves as “a primary determinant of health and disease” [12]. Physical literacy thus focuses on skill acquisition. In this way, it is similar to the construct of health literacy, which inculcates the ability to find, understand, evaluate, and apply health information and therefore combines knowledge with motivation and competence [13, 14]. To date, no intervention combining physical literacy with community-based strategies has been conducted. Therefore, the StuPs project aims to close this gap between science and practice by implementing a participatory and interdisciplinary multicomponent approach targeting both schools and communities in two socially deprived areas in Cologne (North Rhine-Westphalia, Germany) within the scope of capacity building for physical literacy promotion.

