
## Methods

### Study design

The StuPs design (Fig. 1) is intended to function as a temporary supporter of the selected districts over the project duration of three years, divided into two periods. The first period (Period I) will be conducted over the course of 9 months. Using a multicomponent, mixed-methods approach, it will identify structures like geographic information system data (GIS), existing capacities, collaborations, and networks to detect needs and wants regarding physical activity promotion in children. At the end of this period, required actions will be deduced. With the knowledge of these required actions, measures to create healthy environments in the sense of capacity building and physical literacy promotion in children will be developed. This procedure will be conducted with the participation of key stakeholders in the two Cologne districts. The intention is to create measures integrable into the routines of the stakeholders, schools, and target group and address individuals as well as their environments. Therefore, these measures will on the one hand address the behaviors of children and their families as well as their districts’ capacities to create healthy environments. On the other hand, they will enable local stakeholders within the topic of health and physical literacy promotion by qualification trainings.

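### With no comparison group described, a pre/post difference in mean physical literacy includes any normal development in retested children and cannot be read as programme effect

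*Protocol article*

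**What the plan says.** The abstract's Methods paragraph says of Period II that "the measures will be applicated, implemented and evaluated using a pre−/post-design to assess efficacy". The Study design section repeats the contrast for the children: "To investigate behavioral changes, pre- and post-tests of the children’s physical literacy levels will be conducted". It gives the length of the period that holds these tests: "The intention of the second period (Period II) is to implement the developed measures over a 27-month period". The test dates are not given.

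Under Participants and recruitment, two elementary schools are recruited, one per district, and every child there may take part. The approach is called partly randomised, but nothing is allocated to arms and no comparison school or district is mentioned.

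The Data management and analysis section says how change is to be found: "Descriptive analysis will be conducted to identify cross-sectional and long-term changes in physical literacy level, including motor skills, by generating means and variances". The next sentence adds analysis of covariance and regression to study associations and influencing factors. It names no covariates. The same section sets the significance level at .05 and says that assessments are anonymous. The Discussion lists age, gender, motor skills and psychosocial development as personal factors in physical literacy.

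**The concern.** Without a concurrent comparator, elapsed time and exposure to the measures coincide. In children of elementary school age, time alone can be expected to move motor skills and other components of physical literacy, and the protocol accepts age as a factor. A difference between post-test and pre-test means in the same children is then the sum of development and programme effect, and means and variances cannot separate the two.

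The protocol plans a transfer guideline for other districts at the end of Period II, which is to serve as a model of good practice. If developmental gain were taken for efficacy, that guideline could recommend measures whose effect on the children was never isolated.

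**Working it through.** **Timeline.** The study design states: "The first period (Period I) will be conducted over the course of 9 months". With Period II, 9 + 27 = 36 months, which agrees with the stated three years. The abstract and the study design place the pre- and post-tests in Period II, so 27 months (27/12 = 2.25 years) is a ceiling on the interval, not its stated value.

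**What the difference contains.** Let g be growth in SD per year, T the interval in years and d the programme effect. For retested children, the expected mean change is g × T + d. Adding baseline age gives change = (g × T + d) + b × (baseline age − mean age). The covariate explains differences between children, but the intercept is still g × T + d. Adjusting for baseline age alone therefore does not remove a shift common to all children. A term for age at test could help, because the spread of ages within each wave carries information on g.

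**Illustration of size.** The protocol gives no sample size, growth rate, SD or correlation, so there is no figure of its own to reproduce. All inputs below except the 27-month ceiling and the .05 level are assumptions, and the test is taken as two-sided.

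- Drift = g × months/12, with d = 0.
- SE = sqrt(2(1 − r)/n) in SD units, with n children per wave and r the pre/post correlation (r = 0 represents unlinked records).
- P(p<.05) = 1 − Φ(1.96 − drift/SE) + Φ(−1.96 − drift/SE).

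Lowest case at 27 months and 0.1 SD per year: drift = 0.1 × 2.25 = 0.225; n = 50, r = 0; SE = sqrt(2/50) = 0.200; drift/SE = 1.125; P = 0.20.

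Highest case, same growth and interval: n = 200, r = 0.7; SE = sqrt(0.6/200) = 0.055; drift/SE = 4.11; P = 0.98.

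All cases at 27 months and 0.1 SD per year:

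| n | r = 0 | r = 0.5 | r = 0.7 |
|---|---|---|---|
| 50 | 0.20 | 0.36 | 0.54 |
| 100 | 0.36 | 0.61 | 0.83 |
| 200 | 0.61 | 0.89 | 0.98 |

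Dependence on interval and growth, with n = 100 and r = 0.5 (SE = sqrt(1/100) = 0.100):

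| Growth per year | 6 months | 12 months | 27 months |
|---|---|---|---|
| 0.1 SD | 0.08 | 0.17 | 0.61 |
| 0.2 SD | 0.17 | 0.52 | 0.99 |
| 0.3 SD | 0.32 | 0.85 | 1.00 |

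With drift removed, the probability is 0.05 in every cell.

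**The case against.** Several stronger readings are tempting, and the document does not support them.

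- **That raw scores are compared.** The text says means and variances but not of which score. Age-normed scores are neither stated nor excluded, and the third intervention-mapping step still plans a search for instruments.
- **That the same linked children are retested.** This is the more natural reading of pre- and post-tests, but it is not stated. Assessments are anonymous, linkage is not described, and the analysis sentence mentions cross-sectional as well as long-term change. If each wave tests whoever is then enrolled, mean age need not shift. It therefore cannot be said flatly that the evaluation would show improvement from ineffective measures.
- **That ageing would hide a benefit on activity.** The Background says that "time spent physically exercising correlates positively with socioeconomic status and negatively with age", but this comes from survey data on exercise time. The stated child outcome is physical literacy including motor skills, and no activity-time measure is described for the child tests.
- **That the two tests fall in different seasons.** This needs tests at both ends of Period II, and no dates are given.
- **That the whole evaluation fails.** Structural change is assessed separately by repeating the Period I analysis, and there is an external evaluation. Neither rests on the children's scores.

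The planned covariance and regression analyses also count for the other side, since a covariate list is normal content for a fuller plan. But the text gives them a different task, and baseline age as a covariate would not cure the problem. Finally, the quoted analysis is called descriptive and no test of change is specified, so the rejection rates illustrate a test that the protocol does not define.

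These points limit the size and certainty of the problem. They leave the core standing: the abstract ties the pre/post contrast to efficacy, no comparator is described, and the stated way of identifying change cannot support that claim in retested children.

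**Conclusion.** The point holds in conditional form. If the same children are retested on scores that are not age-referenced, the pre/post difference in means includes normal development and is not an estimate of programme effect. The structure of the design is enough for that conclusion; no assumed number is needed.

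The size is uncertain. It ranges from little (about 0.08 against a nominal 0.05 over 6 months, at 0.1 SD per year with n = 100 and r = 0.5) to near-certain false significance over 27 months in larger, well-correlated samples. Growth, n, r and the interval all have to be assumed. If scores are age-normed, or if each wave is a fresh sample with the same age structure, the bias largely disappears, and a sentence saying so would settle the matter.

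**What to change.** In Data management and analysis:

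1. Record age in months, grade and sex at each test.
2. Estimate change on age- and sex-referenced scores where the instrument has norms. Otherwise compare post-test pupils with pre-test pupils of the same grade within school, or fit a model with age at test that uses the age spread within each wave.
3. If within-child change is analysed, link the two tests by a pseudonymous code and reconcile this with the anonymity statement.
4. State that unadjusted pre/post means describe change over time and are not evidence of efficacy, and align the abstract's wording.
5. State the limits of the same-grade contrast: it is a historical control, open to secular and cohort differences, and it includes pupils with shorter exposure to the measures.

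Holding both tests in the same calendar month is optional.

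The cost is a few routinely known variables, a code if records are linked, some wording, and slightly less precision than a paired difference. For the same-grade contrast, the grades to be compared must already be covered at the pre-test; this cannot be recovered later.
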